## 5. **CONSENT**

It will be the responsibility of the Investigator to obtain written informed consent for each participant prior to performing any trial related procedure. In the majority of cases the participants will be consented by the clinical research fellow listed on the delegation log. Taking of consent may be delegated to other medically qualified members of the research team.

A Participant Information Sheet (PIS) will be provided to participants. The Investigator or delegate(s) will ensure that they adequately explain the aim, trial treatment, anticipated benefits and potential hazards of taking part in the trial to the participant. They will also stress that participation is voluntary and that the participant is free to refuse to take part and may withdraw from the trial at any time. The participant will be sent the PIS in the post as a part of the invitation, allowing the participant the opportunity to consider their participation in the trial. A screening appointment will be made at which the participant will have the opportunity to ask any questions. If the participant expresses an interest in participating in the trial they will be asked to sign and date the latest version of the Informed Consent Form (ICF). The consent form will ask the patient to provide explicit consent for the regulatory authorities, members of the research team and or representatives of the sponsor to be given direct access to their medical records and this will be reflected in the consent documentation.

The Investigator or delegate will then sign and date the form. A copy of the ICF will be given to the participant, a copy will be filed in the medical notes, and the original placed in the Investigator Site File (ISF). Once the participant is entered into the trial, the participant's trial number will be entered on the Informed Consent Form maintained in the ISF.

Details of the informed consent discussions will be recorded in the participant's medical notes. This will include date of discussion, the name of the trial, summary of discussion, version number of the PIS given to participant and version number of ICF signed and date consent received. Participants will be advised that data from their QoL questionnaires will not be used directly to inform their clinical care and that if they have any concerns regarding their well-being that the participant should raise this directly with their clinical team. Throughout the trial the participant will have the opportunity to ask questions about the trial. Any new information that may be relevant to the participant's continued participation will be provided. Where new information becomes available which may affect the participants' decision to continue, participants will be re-consented. The participant's right to withdraw from the trial will remain.

Electronic copies of the PIS and ICF will be available from the PC-CRTU trials team and the header will contain details of the local institution. Details of all participants approached about the trial will be recorded on the Participant Screening/Enrolment Log and with the participant's prior consent, their General Practitioner (GP) will also be informed that they are taking part in the trial.

---

|                          |            |               |            |       |          |
|--------------------------|------------|---------------|------------|-------|----------|
| Trial name:              | IMPRESS-AF |               |            |       |          |
| Protocol version number: | 6.0        | version date: | 12/10/2015 | Page: | 21 of 67 |

## 6. ENROLMENT AND RANDOMISATION

### 6.1 Enrolment

#### Screening:

- Informed consent taken
- Eligibility criteria will be checked with the participant.
- Brain Natriuretic Peptide (BNP) level test using point of care device
- BP measurement
- If the participant has had blood tests performed at City Hospital within the 30 days preceeding the screening visit, results from these tests will be used for assessment at screening. If the results are abnormal and there is a clinical reason to repeat or no results are available for the patient, blood samples will be taken and the following tests performed: renal function, potassium, sodium, HBA1c (for diabetic patients only), lipid levels and full blood count (including hematocrit)
- Echocardiogram and ECG will be performed

### 6.2 Randomisation

Patients meeting all eligibility criteria and providing written informed consent will be randomised at the baseline visit. Participants will first be stratified on the basis of their baseline peak  $VO_2$  (two stratification groups;  $VO_2 \leq 16$  ml/min/kg, and  $VO_2 > 16$  ml/min/kg). A secure web-based randomisation system will be used to allocate a unique investigational medicinal product (IMP) number to each participant.

The randomisation process will use two lists. The first list (the Randomisation List) comprises two stratification groups for patients with peak  $VO_2 \leq 16$  ml/min/kg and peak  $VO_2 > 16$  ml/min/kg, with a total number of 256 rows per stratification group (to allow for the hypothetical possibility that all trial participants could fall into the same stratification group). Each row will be marked as 'A' or 'B', referring to treatment A or treatment B respectively. A block randomisation approach will be taken, whereby each stratification group is divided into blocks of four rows, with both A and B occurring twice within every block of four (i.e. AABB, ABAB, ABBA, BBAA, BAAB and BABA). This will ensure that the number of A's or B's can only differ by a maximum of two within any sequence of randomisation within each stratification group (the number of A's and B's will usually be the same or one apart). The randomisation process will work through the relevant stratum of the Randomisation List in a sequential order, to assign each patient to treatment A or B. The second list (the IMP Number List) consists of the unique numbers 001P to 250P in a random order, and assigned randomly to A or B, but in a 50:50 ratio. Upon determination of A or B from the Randomisation List, the computer will select a unique number from the corresponding group in the IMP Number List. This number will be assigned to the newly randomised patient, who will then be supplied with the medication bottle with the matching number.

The online randomisation described above will be incorporated into a secure bespoke trial database; however contingency has been planned for paper-based randomisation in the unlikely event of a temporary system failure. A telephone back up will be available via the PC-CRTU randomisation line, which will be staffed Monday to Friday during office opening hours.

### 6.3 BLINDING

Trial participants, the trial team in contact with the patient, care providers, outcome assessors and data analysts will all remain blinded to the treatment after assignment to interventions.

Blinding of the trial drug identity will take place at the time of packaging and labelling. The trial drug will be overencapsulated and packaged by Catalent Pharma Solutions, who will be supplied with the IMP Number List by the PC-CRTU computer programmer. The IMP Number List will also state which of A or B represents the spironolactone, and which the placebo, and Catalent Pharma Solutions will use this information to label the medication bottles accordingly. Overencapsulation and bottle labelling will be performed in one run for spironolactone and a completely separate run for placebo. Medication bottles will be labelled only with the unique IMP number, and the label will not indicate whether the contents are active or placebo. Catalent Pharma Solutions will also produce six spare bottles of trial medication (three each of spironolactone and placebo, randomly assigned by the computer programmer to IMP Numbers 251P-256P). In the event of a patient losing their medication, the computer will allocate to that patient another number corresponding to a spare medication bottle for the same trial arm.

Only the computer programmer and Catalent Pharma solutions will see the IMP Number List (and thus be unblinded to the trial arms), however 256 individually numbered security-sealed envelopes, each containing the respective codebreak, will also be supplied to the Pharmacy Department at City Hospital (who are independent of the trial, and operate 24 hours a day). City Hospital Pharmacy Department will be responsible for unblinding in the event of an emergency codebreak situation occurring. Codebreaks of the trial drug will be restricted to emergency situations only; these will be rare, as any sick patient will be treated symptomatically, and their management will not usually be altered by knowing the identity of the trial compound (i.e. spironolactone or placebo). Unblinding should be avoided unless knowledge of the trial treatment is essential for the correct clinical care of the patient, e.g. in the cases of acute liver injury, acute renal failure, Stevens-Johnson syndrome or agranulocytosis, if suspected to have been caused by spironolactone. Cases that are considered serious, unexpected and possibly, probably or definitely related will be unblinded.

In the event of a codebreak situation occurring, City Hospital Pharmacy Department will be alerted and will follow the instructions on the codebreak form; all fields must be completed before performing the codebreak. The PC-CRTU should be informed as soon as possible if the code has been broken. This must be done by sending a copy of the completed codebreak form to the PC-CRTU via email or fax. The codebreak envelope must also be resealed as soon as possible; the time and date of the codebreak should be documented, along with the name of the person performing the codebreak, and the reason for the codebreak.

Once the code is broken, the patient will be withdrawn from the trial treatment, as they will become unblinded to their trial drug. However, where applicable, these patients will be asked to complete the QoL questionnaires at the 12 month and 24 month visits. Please refer to the patient withdrawal section for more information.

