### 7.2 Treatment and Dosing Schedule

Trial participants will receive either Spironolactone or matched placebo according to the following instructions:

- a single 25 milligram tablet
- to be taken orally once per day (typically to be taken during the morning, but can be taken regularly at other time of day if preferable).
- to be taken with a drink to help swallowing of the drug
- for a 24 month period

In the case of an increase in potassium level to 5.1-5.5 mmol/L or in the presence of other non-life-threatening side effects (such as gynaecomastia), the trial drug will be down-titrated to 25 mg each second day. In such cases, the investigators are advised to re-up-titrate the trial medication if the reason for down-titration has resolved. Routine laboratory surveillance of serum potassium, sodium, full blood count with hematocrit, and renal function will be done by protocol at each visit and within 1 week of any dose adjustment.

Drug toxicity will be defined as an increase in potassium level to >5.5 mmol/L. In the case of toxicity or suspected toxicity, the trial medication will be stopped for the duration of the trial, but the patient will be requested to attend the remaining follow up visits.

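### Section 6.3 does not separate unblinding for a safety report from a disclosed emergency codebreak, and asks patients withdrawn after a codebreak only for quality-of-life questionnaires

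*Protocol*

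**What the plan says.** Section 6.3 opens with a general commitment. Besides the participants themselves, "the trial team in contact with the patient, care providers, outcome assessors and data analysts will all remain blinded to the treatment". It goes on: "Codebreaks of the trial drug will be restricted to emergency situations only". Later in the same paragraph comes a rule with no condition of clinical need: "Cases that are considered serious, unexpected and possibly, probably or definitely related will be unblinded".

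The procedure that follows is the sealed-envelope codebreak run by the City Hospital pharmacy, with a form that is copied to the trials unit. The consequence is then given: "Once the code is broken, the patient will be withdrawn from the trial treatment, as they will become unblinded to their trial drug". On follow-up, 6.3 says that, where applicable, "these patients will be asked to complete the QoL questionnaires at the 12 month and 24 month visits", and it refers the reader to the withdrawal section.

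That section (8.4) and the Additional Visits text in 8.3 also name only quality of life at months 12 and 24 for patients who stop medication but stay in the trial. Section 7.2 is wider. After toxicity or suspected toxicity the drug is stopped, but "the patient will be requested to attend the remaining follow up visits".

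**The concern.** Unblinding a SUSAR for the authorities and breaking the code to treat a sick patient are different acts. The first can be done inside the trials unit without the patient or the site learning anything. The second normally tells the treating team what the patient was taking. Section 6.3 gives one procedure and one consequence and does not say which act they cover. The reason it gives for stopping treatment is that the patient knows the allocation, not that stopping is clinically needed. That reason need not hold when the code is opened only for a report.

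Two things are at stake. A participant in either arm could lose allocated treatment because of an administrative step, even if the reaction had resolved or the code showed placebo. And the patients concerned are asked in terms only for questionnaires, although the primary outcome is an exercise test at 2 years analysed by intention to treat.

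**Working it through.** This is mainly a comparison of text, with a short calculation of scale.

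**Unblinding and withdrawal**

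1. Trigger. The rule in 6.3 that serious, unexpected, related cases are unblinded matches the SUSAR definition in section 20. It is mandatory and does not depend on the patient's clinical need.
2. Route. The only route described in 6.3 is the pharmacy envelope, and the pharmacy's responsibility is for emergencies. The trials unit's programmer already holds the allocation list but is given no role in SUSAR reporting. Sections 9.5.2, 9.6 and 9.7.1 cover classification and reporting times, but not who obtains the allocation or who stays blinded.
3. Consequence. Withdrawal follows once the code is broken. Section 6.3 uses the terms codebreak and unblinding without defining a difference, so a site could take step 1 as meeting the condition in step 3.

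**Follow-up after treatment stops**

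| Situation | Section | What is requested |
|---|---|---|
| Code broken | 6.3 | Quality of life, months 12 and 24 |
| Voluntary withdrawal from treatment | 8.3 | Quality of life, months 12 and 24 |
| Withdrawn from medication | 8.4 | Quality of life, months 12 and 24 |
| Toxicity or suspected toxicity | 7.2 | Attend remaining follow-up visits |
| All participants | 8.1, 8.3 final visit | Full visit, including the exercise test |

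The last row has no on-treatment condition, but it is not carried over to the patients in the first three rows. Section 2.2 makes peak VO2 at 2 years the primary endpoint, and 13.1 specifies intention to treat.

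**Scale**

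The inputs come from 13.1.1: 250 randomised, 200 to be retained, difference 2, SD 5, two-sided 5%.

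- The plan's power reproduces by two-sample t-test: 80.4% at 100 per arm (stated 80%) and 88.3% at 125 per arm (stated 88%).
- One case off allocated treatment: 1/250 = 0.4% of the trial, or 1/125 = 0.8% of an arm.
- Planned loss allowance: 250 − 200 = 50. If the month-24 exercise test were missed, one case would use 1/50 = 2% of it.
- The protocol gives no SUSAR rate. As an illustration only, missing tests on top of all 50 planned losses would give power of 80.2% for 1 extra, 79.4% for 5 and 78.3% for 10.

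**The case against.** The strongest reply is that the withdrawal sentence closes a passage about emergency codebreaks and carries its own limit: it applies because the patient becomes unblinded. If the patient never learns the allocation, the ground is absent. The opening of 6.3, which keeps participants and the trial team blinded, supports that reading. This has force. A reader might infer that the protocol definitely removes participants from treatment because of a reporting step. The text does not establish that; it leaves the matter open.

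A reader might also infer that the month-24 exercise test is dropped for these patients. The documents do not say so. They leave trial treatment, not the trial; the month-24 questionnaire is tied to a visit; and 8.1 and the final-visit list in 8.3 include the exercise test for participants generally. A patient who also meets the toxicity rule in 7.2 would be asked to attend anyway. What stands is that the specific instructions name less than the general ones and less than 7.2.

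It would be a further overreach to say that 9.7.4 discloses allocation to Principal Investigators. It refers only to details of SUSARs and does not state that allocation is among them. Section 9.8 was not available to this review, so a reporting-only route there cannot be excluded, but 6.3 does not point to one.

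Finally, 6.3 expects codebreaks to be rare, and 9.3.1 treats several known effects of the drug as expected, which narrows the pool of SUSARs. That is a fair argument about size, and it is accepted.

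**Conclusion.** The point holds as an ambiguity with a practical consequence. Section 6.3 mandates unblinding of SUSARs, describes only the pharmacy codebreak, and stops treatment for a reason that need not apply to unblinding done for a report. For the patients withdrawn, the only follow-up it names omits the primary outcome test.

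Severity is minor. The effect is 0.4% of randomised participants per case, in a trial where few cases are expected, and no stated power figure changes. This rests on three assumptions: that SUSARs are few (no rate is given), that any missed tests fall within the 20% loss allowance, and that no unseen text supplies a reporting-only route. The reason to act is less the numbers than that a participant should not leave treatment, or miss the primary assessment, through loose wording.

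**What to change.** - In 6.3, state that for a SUSAR the already unblinded trials-unit programmer supplies the allocation for the regulatory report only, that site, participant, outcome assessors and analysts stay blinded, and that this is not an emergency codebreak.
- In 6.3, limit the withdrawal sentence to codebreaks disclosed to the participant or the treating team.
- In 6.3 and 8.4, ask patients withdrawn from trial medication who remain in the trial to attend all remaining visits, including the month-24 exercise test, in line with 7.2. The matching sentence in 8.3 should follow.

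The cost is a few sentences and a short task for the programmer per SUSAR. The visits are already scheduled for every participant. The downside is that the site manages a SUSAR blinded unless it requests an emergency codebreak on clinical grounds, and that route stays open.

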### 6.4 MECHANISTIC SUBSTUDIES

The blood samples collected during the study visits may be used or stored for future use within the study centre at City Hospital for other ethically approved research projects if relevant consent provided by the patient (Appendix 1).

|                          |            |               |            |       |          |
|--------------------------|------------|---------------|------------|-------|----------|
| Trial name:              | IMPRESS-AF |               |            |       |          |
| Protocol version number: | 6.0        | version date: | 12/10/2015 | Page: | 23 of 67 |

## 7. TRIAL TREATMENT / INTERVENTION

### 7.1 Treatment Supply and Storage

#### 7.1.1 Treatment Supplies

The treatment will be manufactured by Catalent Pharma Solutions and will be shipped directly to the University of Birmingham Centre for Cardiovascular Sciences, City Hospital, [name]. The drug will be produced and delivered in a single batch (as per submitted contract) but if required, this can be negotiated to be produced and delivered in separate batches. Oversight of the drug shipping and handling will be coordinated and managed by the University of Birmingham Centre for Cardiovascular Sciences, City Hospital, [name].

#### 7.1.2 Packaging and Labelling

Catalent Pharma Solutions will also be responsible for the packaging and labelling of the treatment. Placebo and spironolactone will be identical in appearance and packaging and manufactured as 25-mg tablets in accordance with national and international standards.

Sample label:

|                                                                                                                                                                                                                                                                                                                                                                                                                                                                                                                                                                                                                                                                                                     |                                                                                   |
|-----------------------------------------------------------------------------------------------------------------------------------------------------------------------------------------------------------------------------------------------------------------------------------------------------------------------------------------------------------------------------------------------------------------------------------------------------------------------------------------------------------------------------------------------------------------------------------------------------------------------------------------------------------------------------------------------------|-----------------------------------------------------------------------------------|
| 
Subject code: XXXX
 
Batch Number: XXXXXXXXXXXX
 
Expiry Date: DD/MM/YYYY
 
Quantity of capsules in each container: XXXX
 
For clinical trial use only
 
Patient name: _____
 
Date of Supply: _____
 
Directions: one capsule per day or as directed
 
Product: Spironolactone 25mg or placebo
 
Storage conditions: Store in a dry, dark place below 25°C
 
Keep out of the reach of children
 
For use in IMPRESS-AF trial (EudraCT number: 2014-003702-33)
 
Investigator: [name]; Sponsor: University of Birmingham
 
Study Telephone number for all enquiries: [name]
 | [figure not shown] |
|-----------------------------------------------------------------------------------------------------------------------------------------------------------------------------------------------------------------------------------------------------------------------------------------------------------------------------------------------------------------------------------------------------------------------------------------------------------------------------------------------------------------------------------------------------------------------------------------------------------------------------------------------------------------------------------------------------|-----------------------------------------------------------------------------------|

#### 7.1.3 Drug Storage

The drug will be stored in a dedicated storage facility within the University of Birmingham Centre for Cardiovascular Sciences Clinical Trials Unit. The main hospital pharmacy will have oversight. The drug will be stored in a secured room, which meets storage requirements and is compliant with GCP regulations. Checks will be performed, in line with GCP guidelines, including temperature control logs and an SOP detailing temperature excursions, annual audits from pharmacy, secure storage area and limited access.

Any remaining drug at the end of the trial, or returned drug from patients who have withdrawn, will be disposed of by the Centre for Cardiovascular Sciences in conjunction with the NHS pharmacy. The Pharmacy waste disposal will be done using sealed containers prior to incineration off site (Company SITA)

|                          |            |               |            |       |          |
|--------------------------|------------|---------------|------------|-------|----------|
| Trial name:              | IMPRESS-AF |               |            |       |          |
| Protocol version number: | 6.0        | version date: | 12/10/2015 | Page: | 24 of 67 |

